#### Lymphocyte subset and biomarker analysis

A detailed lymphocyte subset analysis will be performed to determine the change in percentage of Treg cells (CD3^+^ CD4^+^ CD8^-^ CD25^high^ CD127^low^) between low-dose IL-2 and placebo throughout the treatment period using flow cytometry. Other lymphocyte subsets will also be assessed in a similar manner.

The change in serum cardiac biomarkers will be evaluated by blood sample analysis at various time points in the trial. These will include high-sensitivity troponin I (hs-Trop I), hsCRP and IL-6. hsCRP at screening and all hs-Trop I measurements will be analysed by the Department of Biochemistry/Clinical Immunology at CUH. All other biomarkers will be analysed by the Core Biochemical Assay laboratory, Cambridge, UK.

Categorical variables will be reported as percentages and counts. All continuous variables will be reported as mean, median, SD, minimum and maximum values. The full analysis population will include all patients who received the trial drug or placebo and completed the treatment course after randomisation.

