We plan to recruit 60 patients for the IVORY study. The sample size is based on an absolute difference of 0.2 in the primary endpoint (mean maximum target to background ratio (TBR_max_) in the index vessel) between placebo and active treatment at the end of the dosing period. This is equivalent to a 10% difference from a reference value of 2.02 and equivalent to the size effect observed after atheroprotective therapy.^35–37^ This is based on the results of previous studies that have reported less than a 10% difference in mean TBR_max_ in the index vessel between active treatment and placebo and failed to reduce cardiovascular outcomes.^34 39 41–43^

Assuming an SD of 0.24, 24 patients per arm, testing at two-sided 5% significance level, would provide 80% power. Therefore, a sample size of 30 completed patients per arm was selected to account for participant dropout and poor-quality scans deemed to be unsuitable for analysis (eg, because of motion artefact). This sample size of n=30 per group also allows the detection of a baseline-corrected 6% difference in TBRmax in the index vessel for the trial primary endpoint (mean 0.125, SD 0.166) between placebo and active treatment at the end of the treatment period, at 2-sided 5% significance level and 80% power.

The study opened on 26 August 2020. Thirty-three participants have completed the trial to date, and we expect recruitment to be completed by December 2023, after which the data analysis will commence.

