**Figure 2 F2:**
[figure not shown]
IVORY trial visits—timeline and assessments. ECHO, echocardiogram; ^18^F-FDG, 2-deoxy-2-[fluorine-18] fluoro-D-glucose; IMP, investigational medical product; PET, positron emission tomography.

During the maintenance phase (V8–V14), participants will be dosed once weekly. These visits will last for 1–1.5 hours. They will be similar to the induction phase visits; however, administration of the IMP will only occur once safety bloods taken during the visit are checked. Cardiac biomarkers and lymphocyte subsets will be measured during alternate maintenance visits (V8, V10, V12, V14). Within approximately 1 week from the completion of dosing, a second postdose ^18^F-FDG PET/CT scan will be undertaken. The final encounter will take place approximately 4 weeks after the final dosing visit via telephone unless an in-person visit is necessary for clinical or safety reasons.

Patients will be withdrawn from the trial after recruitment if any of the prespecified general, cardiac, renal or liver withdrawal criteria are met. They will also be withdrawn from the trial if they are positive for COVID-19 during dosing. The withdrawal criteria are summarised in table 1.

**Table 1 T1:** IVORY study withdrawal criteria

General	Cardiorespiratory arrest. Failure to attend two scheduled dosing appointments without adequate reason based on the PI assessment. Severe hypersensitivity reactions will preclude any further IMP administration. New seizure activity/coma. Severe lethargy or somnolence. Respiratory insufficiency requiring intubation. Pregnancy. Withdrawal of consent. PI discretion. Any serious adverse reaction (AR) or adverse reaction which is deemed by investigators to be severe AR. Any significant incidental finding on PET/CT scan clinical governance reports, which in the opinion of the PI, necessitates further investigation and management. Any medical history, clinically relevant abnormality or reason that is deemed by the PI to make the patient ineligible to continue the trial.

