### Outcome measures and analysis

#### Image analysis

The table above lists the endpoints for this study (table 2). The primary endpoint in this study will be the change in vascular inflammation as measured by mean TBR_max_ in the index vessel on ^18^F-FDG PET/CT scans from baseline to follow-up. This will be calculated by demarcating a region of interest (ROI) including arterial wall and lumen on each axial slice of artery (ascending aorta and both carotid arteries) on the coregistered PET/CT scan and maximum standardised uptake values recorded. Subsequently, ROIs will be normalised by the blood pool ^18^F-FDG concentration in the superior vena cava or jugular vein (for carotids) and averaged to yield an arterial mean TBR_max_ as a quantitative measure of arterial tracer uptake. The ‘index vessel’ defined as the arterial territory with the highest mean TBR_max_ at baseline will be the primary outcome variable.^40^ The change in mean TBR_max_ will be calculated for each index vessel from baseline to follow-up and compared between the treatment groups.

**Table 2 T2:** IVORY study endpoint

Primary endpoints	Change in vascular inflammation (as measured by mean TBR_max_ in the index vessel) on ^18^F-FDG PET/CT from baseline to follow-up scans.
Secondary endpoints	Change in mean TBR_max_ in each arterial region individually restricted to those slices with TBR >1.6. Change in lymphocyte subsets between low-dose IL-2 and placebo. Change in percentage of Treg cells between low-dose IL-2 and placebo. The safety and tolerability of extended dosing of IL-2 in patients with ACS will be evaluated.
Exploratory endpoints	The change in serum cardiac biomarkers (eg, hsCRP, troponin, interleukin 6). Change in ejection fraction as measured on transthoracic echocardiograms. Change in phenotype and function of peripheral blood mononuclear cell subsets (such as B lymphocytes and natural killer cells) as assessed by flow cytometry, gene expression and in vitro activation and suppression assays.

ACS, acute coronary syndrome; ^18^F-FDG, 2-deoxy-2-[fluorine-18] fluoro-D-glucose; hsCRP, high-sensitivity C reactive protein; IL-2, interleukin 2; PET, positron emission tomography; TBR_max_, maximum target to background ratio; Treg cells, regulatory T cells.

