### Adverse event (AE) reporting

Safety and tolerability of low-dose IL-2 in the ACS population will be monitored throughout the course of the study. All AEs will be documented, and a medical doctor blinded to the treatment allocation will determine the causality of each in conjunction with the trial Principal Investigator. AEs, adverse reactions (ARs), serious AEs/serious ARs (SAEs/SARs) and suspected unexpected SARs will be defined as per the International Conference on Harmonisation definitions. SAEs, SARs, suspected unexpected serious adverse reactions will be subject to expedited reporting as per the Medicines and Healthcare products Regulatory Agency guidelines. Severe ARs and SARs will also be documented on a separate log, as these are part of the trial stopping criteria. For all AEs, an assessment of severity, date of onset and resolution will be also documented. Abnormal laboratory results will only be documented as AEs if they are deemed to be of clinical significance.

An independent data monitoring committee (iDMC) will be responsible for the review of all unblinded safety data and will meet quarterly for the first year of the trial and every 6 months until the follow-up visit of the last patient. All iDMC meetings will be held without the involvement of the trial team apart from the unblinded statistician. The trial management group will also assess safety in a blinded manner on an ongoing basis during the trial.

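### The full analysis population is defined as treatment completers, so membership can depend on the drug and randomisation no longer protects the efficacy comparison

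*Protocol article*

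**What the plan says.** The only analysis population in the article is at the end of the section on lymphocyte subset and biomarker analysis: "The full analysis population will include all patients who received the trial drug or placebo and completed the treatment course after randomisation". It follows general reporting rules for categorical and continuous variables. The image analysis section, which holds the primary ANCOVA, names no population of its own.

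The Study protocol section states: "Patients will be withdrawn from the trial after recruitment if any of the prespecified general, cardiac, renal or liver withdrawal criteria are met". Among the general criteria, Table 1 lists "Any serious adverse reaction (AR) or adverse reaction which is deemed by investigators to be severe AR" and "Severe hypersensitivity reactions will preclude any further IMP administration". It adds thresholds for QTc, blood pressure, ventricular arrhythmia, creatinine and ALT.

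The follow-up scan is tied to the end of treatment: "Within approximately 1 week from the completion of dosing, a second postdose" PET/CT is planned.

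Table 2 makes safety a secondary endpoint: "The safety and tolerability of extended dosing of IL-2 in patients with ACS will be evaluated". The adverse event section says "All AEs will be documented".

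**The concern.** A full analysis set is meant to keep the randomised groups as intact as possible. This one keeps a patient only if the course was completed, which happens after randomisation and which the drug can influence. An adverse reaction is by definition attributed to the study product, so the serious or severe reaction criterion links exclusion to treatment directly. A patient withdrawn on that ground during the 8 weeks of dosing cannot be in the set.

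The groups compared would then be IL-2 patients who tolerated the course and placebo patients who completed theirs. If those who leave differ in vascular inflammation from those who stay, and leave at different rates by arm, the TBRmax difference mixes a treatment effect with a selection effect. The lymphocyte and biomarker results are affected too. Samples are taken at V3, V7, V8, V10, V12 and V14, and those already collected from a patient who stops early would be discarded.

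**Working it through.** **1. The plan's own figures.** The design targets an "absolute difference of 0.2 in the primary endpoint" with SD 0.24, two-sided 5% and 80% power.
- The two-sample t-test needs 23.6, so 24 per arm (power 80.7%). This reproduces the stated 24.
- The step to 30 per arm implies an allowance of 1 − 24/30 = 20% for dropout and unusable scans together.
- The baseline-corrected statement (difference 0.125, SD 0.166) needs 28.7, so 29 per arm; power at 30 per arm is 81.8%.

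The sample size is sound. The defect lies in who is analysed.

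**2. From the text to the exclusion.** A serious or severe adverse reaction during dosing leads to withdrawal under Table 1. The course is then not completed, so the patient is outside the set. The same chain applies to the cardiac, renal and liver thresholds. Only the reaction criterion is tied by definition to the drug, and it is enough for the argument.

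**3. Illustration A: selection on a correlated tendency to leave.** The documents give no loss rates by arm and no link between leaving and TBR change, so both are assumed. Suppose the fraction p with the highest latent tendency to leave is lost, and that tendency correlates r with a worse TBR change. The mean change among those who stay is then shifted towards benefit by

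SD × r × g(p), where g(p) = φ(z) / (1 − p) and z is the (1 − p) normal quantile.

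The bias in the difference is SD × r × [g(active) − g(placebo)].

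- Loss 30% vs 10%: g = 0.497 and 0.195, difference 0.302.
  - r = 0.3: 0.166 × 0.3 × 0.302 = 0.015, and 0.015 / 0.125 = 12%.
  - r = 0.5: 0.166 × 0.5 × 0.302 = 0.025, and 0.025 / 0.125 = 20%.
- Loss 20% vs 5%: g = 0.350 and 0.109, difference 0.241. Bias is 0.012 (r = 0.3) to 0.020 (r = 0.5).
- Equal loss by the same mechanism: bias is 0.
- If patients who leave have a better TBR change, the sign reverses.

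Type I error for 30% vs 10% loss from 30 per arm leaves 21 and 27 patients. SE = 0.166 × √(1/21 + 1/27) = 0.048. With z = bias / SE, the two-sided rejection rate under no effect, Φ(z − 1.96) + Φ(−z − 1.96), is about 6% (r = 0.3) to 8% (r = 0.5). These normal-approximation figures leave the SD unchanged by selection.

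**4. Illustration B: a simple mean shift.** If a share d of the active arm is excluded and their mean change is k worse than that of active completers, the bias is d × k. With d = 5% to 30% and k = 0.1 to 0.24, it is 0.005 to 0.072, or 2.5% to 36% of the 0.2 target. With d = 20% and k = 0.2 it is 0.04, or 20% of the target. If all that loss is in the active arm, SE = 0.24 × √(1/24 + 1/30) = 0.066 and type I error is about 9%.

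**5. What redefining the set does and does not do.** Planned N is unchanged. Patients withdrawn from the trial will often lack a follow-up scan, and a change-from-baseline ANCOVA omits them under any label. Imputing from arm, baseline TBRmax and ST-elevation status uses the ANCOVA's own terms, so it largely returns the complete-case estimate. It cannot correct leaving that depends on the unobserved change.

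**The case against.** **The sentence sits under the lymphocyte and biomarker heading.** True, but it follows general reporting rules and the imaging endpoint is given no other population. Even on the narrow reading, samples from patients who stop early would be discarded.

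**A condensed article leaves populations to the full protocol or SAP.** That would answer a missing definition. This definition is stated, and it conditions on completion.

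**The size is driven by assumptions.** This stands. A 30% vs 10% split averages 20%, so it spends the plan's entire allowance, which also covers poor scans, on informative dropout concentrated in one arm. Even then type I error reaches only about 8%. The figures show scale and do not predict.

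**Withdrawn patients would have no follow-up scan anyway.** This largely stands. It means that new wording alone does not remove the bias and that the remedy costs more than an edit.

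**Table 1 does not remove patients for every abnormality.** Correct. ALT, QTc and arrhythmia count only beyond set thresholds, and two missed dosing visits count only without adequate reason in the principal investigator's assessment.

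**A reader might infer that severe reactions will vanish from the safety results.** The documents do not support this. Nothing applies the completers set to safety, all adverse events are documented, severe and serious reactions have a separate log, the data monitoring committee reviews all unblinded safety data, and the stopping rule starts from patients dosed. Those provisions cover collection and monitoring rather than final tabulation, so what remains is a precaution.

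**Conclusion.** The point holds for efficacy. The stated full analysis population is a completers set, and the protocol's own withdrawal rules let treatment affect who is in it. That conclusion needs only the text and can be held with high confidence.

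The direction and size of bias cannot be known from the documents. Under assumed 30% vs 10% loss, correlation 0.3 to 0.5 and SD 0.166, it is about 0.015 to 0.025 TBR units (12% to 20% of the 0.125 target), with type I error of roughly 6% to 8%. With balanced loss by the same mechanism it is nil. It would be wrong to read these figures as evidence that the trial's result is biased by this amount.

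For safety the point is conditional only: tabulating in completers would omit patients withdrawn for severe reactions during dosing, but the article does not say this will be done.

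**What to change.** 1. Define the full analysis population as all randomised patients, analysed in the arm assigned.
2. Run the primary ANCOVA on everyone with baseline and follow-up scans, regardless of doses completed.
3. Include the lymphocyte and biomarker samples already available from patients who stopped early.
4. Add a placebo-reference sensitivity analysis for missing follow-up scans. Imputation from the ANCOVA's own terms is not enough by itself.
5. Seek the follow-up scan already planned, where consent and safety allow, in patients who stop dosing early. The protocol should say how this fits with withdrawal from the trial. No change to any withdrawal criterion is suggested.
6. Keep the present set as a per-protocol sensitivity analysis under that name.
7. State that the safety endpoint is tabulated in all patients who received at least one dose.

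These changes should be fixed before unblinding. The cost is wording, some extra analysis and some follow-up work, and the estimate may be slightly diluted by non-adherence. The planned 60 patients need not change.

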### Adverse event (AE) reporting

Safety and tolerability of low-dose IL-2 in the ACS population will be monitored throughout the course of the study. All AEs will be documented, and a medical doctor blinded to the treatment allocation will determine the causality of each in conjunction with the trial Principal Investigator. AEs, adverse reactions (ARs), serious AEs/serious ARs (SAEs/SARs) and suspected unexpected SARs will be defined as per the International Conference on Harmonisation definitions. SAEs, SARs, suspected unexpected serious adverse reactions will be subject to expedited reporting as per the Medicines and Healthcare products Regulatory Agency guidelines. Severe ARs and SARs will also be documented on a separate log, as these are part of the trial stopping criteria. For all AEs, an assessment of severity, date of onset and resolution will be also documented. Abnormal laboratory results will only be documented as AEs if they are deemed to be of clinical significance.

An independent data monitoring committee (iDMC) will be responsible for the review of all unblinded safety data and will meet quarterly for the first year of the trial and every 6 months until the follow-up visit of the last patient. All iDMC meetings will be held without the involvement of the trial team apart from the unblinded statistician. The trial management group will also assess safety in a blinded manner on an ongoing basis during the trial.

#### Trial stopping criteria

For the first 10 patients dosed, if a cumulative total of three SARs or severe ARs are observed the trial will be halted. This will trigger an unscheduled iDMC meeting to review the unblinded trial data to date.

After the 10th patient has commenced dosing, a percentage basis (30%) of patients who experience prespecified events (SARs or severe ARs) will be used to halt the trial and trigger a review by the iDMC. Once the trial has halted, it will only resume after the approval of a substantial amendment to the regulatory authorities that have approved the trial.

### Patient and public involvement

Patient and public representatives were involved in the design of this study protocol. The NIHR Cambridge BRC Communications and PPI/E Department for Patient and Public Involvement reviewed the patient facing documents and their feedback has been incorporated as much as possible.

## Ethics and dissemination

The Health Research Authority and Health and Care Research Wales, UK (19/YH/0171), approved the study. All participants are required to read the patient information sheet in full and give written consent to participate in the trial. Annual reports will be submitted to the research ethics committee in accordance with national requirements. The results will be reported through peer-reviewed journals and conference presentations.
